## **Protocol**

This supplement contains the following items:

1. Original protocol, which was unchanged and only one version exists.
2. Original statistical analysis plan, which was unchanged and only one version exists

## **Protocol Synopsis**

### **Title:**

A multi-center, randomized, parallel-group, open-label, non-inferiority study to compare the efficacy of intravenous immunoglobulin alone and intravenous immunoglobulin plus high-dose aspirin in acute stage of Kawasaki disease for preventing coronary artery lesion (KIAA trial)

### **Objectives:**

Primary objective is to assess whether intravenous immunoglobulin (IVIG) alone as the primary therapy in acute stage of Kawasaki disease (KD) is non-inferior to IVIG plus high-dose aspirin therapy in preventing the development of coronary artery lesion (CAL) at 6-8 weeks.

Secondary objectives are to compare IVIG resistance rate, duration of fever after IVIG, duration of hospitalization, laboratory data, Z score of coronary artery, CAL at 6 months, adverse event (AE) and serious adverse event (SAE) between IVIG alone and IVIG plus high-dose aspirin as the primary therapy in acute stage of KD.

### **Eligibility:**

#### **Inclusion criteria**

1. Male or female, age less than 6 years old
2. Fulfilled the AHA criteria for KD as below:
  - (1) Fever (more than 38.0°C ear temperature)  $\geq$  5 days, and 4 of the 5 following symptoms
  - (2) Diffuse mucosal inflammation (strawberry tongue, dry and fissured lips)
  - (3) Bilateral non-purulent conjunctivitis
  - (4) Dysmorphic skin rashes

(5) Indurative edematous change over the hands and feet, or desquamation over the finger or toe tip

(6) Cervical lymphadenopathy (one or more nodule at least 1.5 cm in diameter)

3. Informed consent form (ICF) signed by the patient or a legal guardian

### **Exclusion criteria**

1. Symptoms not full fit the KD criteria

2. Acute fever for  $\leq 5$  days or  $>10$  days

3. IVIG treatment at other hospital before refers to study site

4. Treatment with corticosteroids, other than inhaled forms, in the previous 2 weeks

5. Presence of a disease known to mimic Kawasaki disease (such as systemic juvenile idiopathic arthritis, Steven-Johnson Syndrome, Macrophage activation syndrome)

6. Previous diagnosis of KD

7. Inability to take aspirin (history of hypersensitivity to aspirin, G6PD deficiency, intolerance to aspirin)

8. Inability to take IVIG (history of allergic reactions for IVIG, allergic reactions when testing dose of IVIG, selective IgA deficiency)

9. Afebrile before enrolment

10. Concomitant severe medical disorders (e.g. immunodeficiency, chromosomal anomalies, congenital heart diseases, metabolic diseases, nephritis, collagen diseases)

11. Suspected severe infectious disease (e.g. sepsis, septic meningitis, peritonitis, bacterial pneumonia, varicella, and influenza)

12. Conditions judged by the investigator as unsuitable for this trial

### **Study treatment:**

Test group: All patients will receive IVIG (2g/kg) in 10-12 hours alone, **without** high-dose aspirin. After fever subsides, low-dose aspirin (3-5mg/kg/day) will be prescribed until 6-8 weeks.

Standard group: All patients will receive IVIG (2g/kg) in 10-12 hours plus high-dose aspirin (80-100mg/kg/day, divided into four doses) till fever subside. After fever subsides, low-dose aspirin (3-5mg/kg/day) will be prescribed until 6-8 weeks.

**Primary endpoint:**

The primary endpoint is CAL rate at 6-8 weeks.

**Sample size estimation:**

A total of 278 patients will be recruited to achieve 250 per-protocol (PP) patients.

### List of abbreviations

|       |                                                |
|-------|------------------------------------------------|
| AE    | Adverse event                                  |
| AHA   | American Heart Association                     |
| CAL   | Coronary artery lesion                         |
| CRF   | Case report form                               |
| CRP   | C-reactive protein                             |
| CTCAE | Common Terminology Criteria for Adverse Events |
| G6PD  | glucose-6-phosphate dehydrogenase              |
| GCP   | Good clinical practice                         |
| ICF   | Informed consent form                          |
| IRB   | Institutional Review Board                     |
| ITT   | Intention-to-treat                             |
| IVIG  | intravenous immunoglobulin                     |
| KD    | Kawasaki disease                               |
| LAD   | Left anterior descending artery                |
| LMCA  | Left main coronary artery                      |
| PP    | Per-protocol                                   |
| RCA   | Right coronary artery                          |
| RCT   | Randomized controlled trial                    |
| SAE   | Serious adverse event                          |
|       |                                                |
|       |                                                |

## **1. Administrative information**

### **1.1 Title**

A multi-center, randomized, parallel-group, open-label, non-inferiority study to compare the efficacy of intravenous immunoglobulin alone and intravenous immunoglobulin plus high-dose aspirin in acute stage of Kawasaki disease for preventing coronary artery lesion (KIAA trial)

### **1.2 Trial registration**

The clinical trial will be registered on ClinicalTrials.gov

### **1.3 Protocol version**

Protocol Number: KCGCTC-001

Version Number: 1.0

Version Date: 20160620

### **1.4 Funding**

An application for funding to support this trial will be made to Chang Gung Memorial Hospital (CPRP).

## **2. Introduction**

### **2.1 Background and rationale**

Kawasaki disease (KD) is an acute febrile systemic vasculitis that was described by Kawasaki et al. in 1974.[1] In developed countries, it is the leading cause of acquired heart diseases in children.[2-3] It mainly affects children younger than five years old, especially in Asian countries. Reported incidence rates in Taiwan, Japan, and Korea ranges from 69 to 213 cases per 100,000 children under the age of five years.[4-6] The most serious complication of KD is the occurrence of coronary artery lesions (CAL), including coronary artery dilatation, coronary artery aneurysm, and coronary artery fistula formation, which may lead to myocardial infarction, sudden death, or ischemic heart disease.[7-8] In our previous published data, 35 of 341 (10.3%) Taiwanese children had CAL formation 8 weeks after disease onset.[9] Although the clinical features of KD are recognizable, its underlying immuno-pathogenetic mechanisms are still under investigation, particularly the culprit for CAL development.[10-12]

Aspirin has been used in the treatment of KD for many years even before the advent of intravenous immunoglobulin (IVIG). Standard treatment for acute phase of KD introduced by American Heart Association (AHA) and American Academy of Pediatrics (AAP) includes IVIG therapy with a single dose of 2 g/kg infusion over 10-12 h plus oral administration of aspirin at high-dose of 80-100 mg/kg/d.[7] Although aspirin has important anti-inflammatory (high-dose) and anti-platelet (low-dose) effects, no prospective study has confirmed that aspirin reduced the incidence of CAL formation. Some reports have shown that the incidence of CAL is highly dependent on the dose of IVIG, but independent of aspirin dose.[13,14] This suggests that only anti-platelet aspirin dose may be adequate during the acute phase of KD. In Taiwanese data, Hsieh et al. reported that high-dose aspirin in the acute stage of KD has no effect on the response rate of IVIG therapy, duration of fever, or incidence of CAL when children are treated with high-dose (2 g/kg) IVIG as a single infusion, despite treatment before or after day 5 of illness.[15] Our recent retrospective study investigated 851 KD patients from two medical centers in Taiwan (Chang Gung Memorial Hospital-Kaohsiung and Kaohsiung Veterans General Hospital).[16] The children were divided into Group 1, IVIG with high-dose aspirin

(n=305) and Group 2, IVIG without high-dose aspirin (n=546). There are no significant differences between groups 1 and 2 in terms of gender ( $p=0.51$ ), IVIG resistant rate (31/305 vs. 38/546,  $p=0.07$ ), CAL formation rate (52/305 vs. 84/546,  $p=0.67$ ), and total hospital days ( $6.3\pm0.2$  vs.  $6.7\pm0.2$ ,  $p=0.13$ ). These retrospective observational data suggest that aspirin offers little additional benefit to IVIG therapy.

There is still no good quality of randomized control trial (RCT) to evaluate whether children with KD should continue to receive high-dose aspirin as part of their treatment regimen. Cochrane Vascular Group reviewed RCTs of aspirin to treat KD in children.[17] The review authors identified only one RCT (multicenter, 3-arms design), from Japan reported in 1991. Furusho et al compared IVIG and aspirin treatment with aspirin alone, and with IVIG alone.[18] The dose of aspirin was 30 to 50 mg/kg/day in three divided doses until the fever had subsided, then 10 to 30mg/kg/day once a day until “the acute reaction had also disappeared.” Children were enrolled if they presented within seven days of the onset of symptoms. Children with recurrent KD and with CAL at presentation were excluded. Children in the two groups (IVIG with aspirin and IVIG alone) did not differ significantly in respect to age at presentation, sex, or time from onset of symptoms to trial entry. The incidence of new CAL prior to 30 days from onset of symptoms were 18.4% (9 of 49) in children receiving IVIG and aspirin and 18.9% (10 of 53) in children receiving IVIG alone. The relative risk (RR) was 0.97 and 95% confidence intervals (CI) was 0.43 to 2.19. The prevalence of CAL at 30 days after the onset of symptoms were 10.2% (5 of 49) in children receiving IVIG and aspirin and 7.8% (4 of 51) in children receiving IVIG alone. The RR was 1.30 and 95% CI was 0.37 to 4.56.

The risk of aspirin therapy in children with KD is considered to be low and appear to be similar to those reported in other settings. However, serious aspirin side effects have been reported in children treated for KD, including hepatic toxicity, gastritis, upper gastrointestinal bleeding, sensorineural hearing loss, and rarely, Reye’s syndrome.[19-22] Considering the risks of drug toxicity and the lack of evidence for preventing CAL formation, the role of high-dose aspirin in the acute phase of KD needs to be reassessed. Therefore, we initiate this multi-center, prospective, parallel-group, open-label, non-

inferiority RCT to investigate whether high-dose aspirin in the acute stage of KD has beneficial effects on the prevention of CAL formation.

## **2.2 Objectives**

### **Primary objective**

- To assess whether IVIG alone as the primary therapy in acute stage of KD is non-inferior to IVIG plus high-dose aspirin therapy in preventing the development of CAL at 6-8weeks.

### **Secondary objectives**

- To compare IVIG resistance rate, duration of fever after IVIG, duration of hospitalization, laboratory data (CBC/DC, GOT/GPT, and C-reactive protein (CRP)), Z score of coronary arteries, CAL at 6 months, adverse event (AE) and serious adverse event (SAE) between IVIG alone and IVIG plus high-dose aspirin as the primary therapy in acute stage of KD.

## **2.3 Trial design**

The trial is designed as a multi-center, prospective, randomized controlled, open-label, non-inferiority trial with two parallel groups to assess the efficacy of IVIG alone for the primary treatment in acute stage of KD. The primary endpoint is defined as the CAL formation at 6-8 weeks. Patients who meet the eligibility criteria are randomly assigned (1:1) to a test group (receiving IVIG alone) or a standard group (receiving IVIG plus high dose aspirin).

#### **3.2 Eligibility criteria**

Eligible patients are those who meet all of the inclusion criteria mentioned below and none of the listed exclusion criteria:

##### **Inclusion criteria**

Patients eligible for the clinical trial must comply with all of the following at randomization.

1. Male or female, age less than 6 years old

2. Fulfilled the AHA criteria for KD as below:

(1) Fever (more than 38.0°C ear temperature)  $\geq$  5 days, and 4 of the 5 following symptoms

(2) Diffuse mucosal inflammation (strawberry tongue, dry and fissured lips)

(3) Bilateral non-purulent conjunctivitis

(4) Dysmorphous skin rashes

(5) Indurative edematous change over the hands and feet, or desquamation over the finger or toe tip

(6) Cervical lymphadenopathy (one or more nodule at least 1.5 cm in diameter)

3. Informed consent form (ICF) signed by the patient or a legal guardian

### **Exclusion criteria**

Patients fulfilling any of the following criteria are not eligible for inclusion in this clinical trial.

1. Symptoms not full fit the KD criteria

2. Acute fever for  $\leq 5$  days or  $>10$  days

3. IVIG treatment at other hospital before refers to study site

4. Treatment with corticosteroids, other than inhaled forms, in the previous 2 weeks

5. Presence of a disease known to mimic Kawasaki disease (such as systemic juvenile idiopathic arthritis, Steven-Johnson Syndrome, Macrophage activation syndrome)

6. Previous diagnosis of KD

7. Inability to take aspirin (history of hypersensitivity to aspirin, G6PD deficiency, intolerance to aspirin)

8. Inability to take IVIG (history of allergic reactions for IVIG, allergic reactions when testing dose of IVIG, selective IgA deficiency)

9. Afebrile before enrolment

10. Concomitant severe medical disorders (e.g. immunodeficiency, chromosomal anomalies, congenital heart diseases, metabolic diseases, nephritis, collagen diseases)

11. Suspected severe infectious disease (e.g. sepsis, septic meningitis, peritonitis, bacterial pneumonia, varicella, and influenza)

12. Conditions judged by the investigator as unsuitable for this trial

## **Withdraw criteria**

Participants should be withdrawn from the clinical trial if any of the conditions set below has occurred. The reason for a patient withdrawn from the study will be recorded in the case report form (CRF) and in the participant's medical record.

1. Participant or his/her legal guardian decides to withdraw his/her ICF.
2. Participant has allergic reaction during IVIG or aspirin treatment.
3. Participant develops AE or SAE that the investigator considered a cessation of the study treatment is necessary.
4. Participant is lost of follow up.
5. Investigator considers that the participant is no longer physically and/or psychologically feasible to remain in the study.

## **3.3 Intervention**

### **● Test group**

All patients will receive IVIG (2g/kg) in 10-12 hours alone, **without** high-dose aspirin. After fever subsides, low-dose aspirin (3-5mg/kg/day) will be prescribed until 6-8 weeks.

### **● Standard group**

All patients will receive IVIG (2g/kg) in 10-12 hours plus high-dose aspirin (80-100mg/kg/day, divided into four doses) till fever subside. After fever subsides, low-dose aspirin (3-5mg/kg/day) will be prescribed until 6-8 weeks.

### **● Concomitant treatment**

The investigators should try to minimize the concomitant treatments for the patient during the study. Any use of concomitant treatment must be recorded on the CRF.

### **● Prohibited treatment**

Use of steroid, anti-TNF, anti-IL6, anti-IL17, anti-CD20 (etc. biologic agents) is not allowed during the study treatment unless the subject has withdrawn from the trial.

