### 3.6 Sample size

The sample size determination is based on the result of our retrospective data.[16] The estimated proportions of CAL are 17% after IVIG and high-dose aspirin combination treatment and 15.4% after IVIG alone treatment. We consider the difference less than 10% is of no clinical importance. The following contents are the statistical basis for estimating sample size for this trial.

$$H_0: P_T - P_S \leq \delta$$

$$H_A: P_T - P_S > \delta$$

$$P_T: \text{CAL-free rate in test group} = 0.846$$

$$P_S: \text{CAL-free rate in standard group} = 0.83$$

$$\delta = -0.1$$

Assume that the type I and type II error rates are  $\alpha = 0.05$ ,  $\beta = 0.2$ , respectively. The clinically meaningful difference  $\delta$  is -0.1. The CAL-free rate of test group (IVIG alone)  $P_T$  is 0.846 and that of standard group (IVIG + high dose aspirin)  $P_S$  is 0.83.

Assume the sample sizes of two groups are equal, the sample size of each group for the non-inferiority trial is 125 patients. Offsetting a maximal dropout of 10%, 139 patients are required for per group. That is, a total sample size of 278 patients is required for the trial.

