### **3.9 Blinding**

Participants and study investigators are unblinded to the group of IVIG alone or IVIG plus high-dose aspirin.

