**Exit Form**

**Exit date:** 20□□/□□/□□

**Complete study:** ☐YES ☐No

**Withdraw:** ☐YES (if YES, choose the cause) ☐No

- ☐ 1. Participant or his/her legal guardian decides to withdraw his/her ICF.
- ☐ 2. Participant has allergic reaction during IVIG or aspirin treatment.
- ☐ 3. Participant develops AE or SAE that the investigator considered a cessation of the study treatment is necessary.
- ☐ 4. Participant is lost of follow up.
- ☐ 5. Investigator considers that the participant is no longer physically and/or psychologically feasible to remain in the study.

|                                                                                                                                                   |                                 |             |
|---------------------------------------------------------------------------------------------------------------------------------------------------|---------------------------------|-------------|
| I have reviewed all data recorded on all pages of this visit and certify that they are accurate, complete and consistent to the subject's record. | Investigator's Signature | Date |
|                                                                                                                                                   |                                 |             |

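### Stopping study treatment, or steroid or biologic rescue, is tied to leaving the trial, and no available text keeps the 6-8-week echocardiogram for these children

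*Combined protocol and SAP*

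**What the plan says.** Section 3.2, Withdraw criteria, opens: "Participants should be withdrawn from the clinical trial if any of the conditions set below has occurred". The five conditions put two treatment-related events, "Participant has allergic reaction during IVIG or aspirin treatment" and "Participant develops AE or SAE that the investigator considered a cessation of the study treatment is necessary", in one list with withdrawn consent, loss to follow-up and the investigator's judgement that staying in the study is not feasible. All five lead to the same outcome, and the section asks only that the reason be recorded.

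Section 3.3, Prohibited treatment, says that steroid or biologic use "is not allowed during the study treatment unless the subject has withdrawn from the trial". Both arm descriptions in section 3.3 run low-dose aspirin to 6-8 weeks, so on a natural reading this rule covers the time up to the primary endpoint.

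Section 3.5 and the week 6-8 form page schedule the echocardiogram without saying whether it is done after withdrawal. The Exit Form offers study completion or withdrawal ("if YES, choose the cause"). It has no entry for a child who is off treatment but still followed.

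Other parts limit the problem. Exclusions 7 and 8 remove children with known intolerance of aspirin or IVIG. IVIG resistance is not a withdrawal criterion, and the treatment form lists a second IVIG dose for it. The case report form also records aspirin start and stop times and concomitant drugs.

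**The concern.** Allergy, toxicity and a need for rescue follow from the treatment or the disease; they are not random dropout. Only the standard arm receives high-dose aspirin, and section 3.9 states that "Participants and study investigators are unblinded to the group". Decisions to stop or rescue may therefore differ by arm. If the outcome is not collected afterwards, the children left for analysis are a selected group, possibly selected differently in each arm.

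The dropout allowance does not address this. It restores the number of evaluable children, not the comparability of the arms. Nor does the SAP's ITT label for the primary outcome, because an analysis by allocated arm cannot use a scan that was never done. At stake are the error rate and power of the non-inferiority comparison.

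**Working it through.** **1. The plan's sample size.** Section 3.6 gives CAL-free rates of 0.83 (standard) and 0.846 (test), a margin of 0.10, alpha 0.05 and power 80%. With unpooled variance and one-sided 5%:

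n = (1.645 + 0.842)² × (0.83×0.17 + 0.846×0.154) / (0.10 + 0.016)² = 124.7, so 125 per arm.

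125/0.90 = 138.9, so 139 per arm and 278 in total. Both match the plan. The sidedness of alpha is not stated. One-sided 2.5% gives 159 per arm, so one-sided 5% is the reading that fits, and I assume it below.

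**2. Room for loss.** The synopsis states: "A total of 278 patients will be recruited to achieve 250 per-protocol (PP) patients". That leaves 278 − 250 = 28 children, or 14 per arm. This covers all causes, so losses through the rules at issue should be fewer.

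**3. Which arm may lose more.** Section 2.1 reports IVIG resistance of 31/305 (10.2%) with high-dose aspirin and 38/546 (7.0%) without (p = 0.07, retrospective), and lists aspirin toxicities. Applied to 139 per arm, this is 14.1 resistant children in the standard arm and 9.7 in the test arm. The plan does not withdraw all of them. I therefore use 10 test and 14 standard as an upper illustration, with about half (5 and 7) and about a quarter (2 and 4).

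**4. Model.** The true CAL risk is at the margin: 27% test, 17% standard. L of 139 children are lost in an arm, and lost children have CAL risk c. The documents do not give c; I use 50% and 30%. The risk among children still observed is

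p_obs = (139p − L·c) / (139 − L).

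Non-inferiority is declared if the one-sided 95% upper Wald bound (unpooled) for test minus standard is below 10 points. The probability is an exact sum over both binomial distributions.

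Examples:
- 10 test and 14 standard lost, c = 50%: test (37.53 − 5)/129 = 25.2%; standard (23.63 − 7)/125 = 13.3%; difference 11.9 points.
- 14 test and 7 standard lost, c = 50%: test (37.53 − 7)/125 = 24.4%; standard (23.63 − 3.5)/132 = 15.3%; difference 9.2 points.
- 14 test and 7 standard lost, c = 30%: test (37.53 − 4.2)/125 = 26.7%; standard (23.63 − 2.1)/132 = 16.3%; difference 10.4 points.

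Probability of false non-inferiority:

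| Lost, test / standard | c = 50% | c = 30% |
|---|---|---|
| 0 / 0 | 5.03% | 5.03% |
| 2 / 4 | 3.82% | 4.35% |
| 5 / 7 | 3.43% | 3.95% |
| 10 / 14 | 2.19% | 3.08% |
| 14 / 14 | 3.20% | 3.20% |
| 7 / 14 | 1.64% | 2.92% |
| 14 / 7 | 7.17% | 4.47% |

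Losing 8% of children in the test arm only, a more extreme imbalance, gives 11.1% at c = 50% and 5.8% at c = 30%.

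**5. Power.** At the planned CAL rates (15.4% and 17%) and c = 50%, power is 83.8% with all 139 per arm observed. It is 81.6%, 82.5% and 80.8% with 2/4, 5/7 and 10/14 lost. The planned 125 per arm gives 80.4% by the same calculation.

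**The case against.** The strongest reply is that this argues from silence. Neither rule cancels the 6-8-week echocardiogram, section 3.5 lists it without exception, and pages not available here, such as the consent form, may provide for data after withdrawal. That stands as a limit: loss is possible, not established. It does not remove the point, because withdrawal from the trial is a stated rule and nothing available keeps the scan afterwards. Recording rescue drugs is not an instruction to continue follow-up.

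A second reply is that few children are affected. Known allergy is excluded, resistance alone does not trigger withdrawal, and no text suggests that steroid or biologic rescue is common. This stands.

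A third is that the larger error rates need an assumed CAL risk about three times the planned 15-17%, together with excess loss in the test arm. This also stands. A tipping example points the same way. With 19/125 test and 21/125 standard children with CAL, the upper bound is 6.0 points. If 2 of 14 lost standard children had CAL, 8 of 14 lost test children would be needed to cross the margin (27/139 against 23/139, bound 10.45); 7 of 14 gives 9.67.

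Finally, under the per-protocol primary analysis of section 3.11 these children would probably be left out even with a scan. That is true, and it limits what the fix can achieve.

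**Conclusion.** The point holds as a design weakness that should be fixed. The rules join stopping treatment to leaving the trial, and some primary outcomes may be lost for treatment-related reasons.

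A reader might infer that this biases the trial towards declaring non-inferiority. The documents do not support that. Their limited evidence, one retrospective comparison and a list of aspirin toxicities, suggests more loss in the standard arm. In that case the false non-inferiority rate falls (3.8% to 2.2% against 5.0% at 50% CAL risk) and power drops by about 1 to 3 points. Inflation to 7.2% needs 14 test against 7 standard children lost at 50% risk; at 30% the same losses give 4.5%. A reader might also infer that every IVIG-resistant child is withdrawn, or that the scan is cancelled; neither is stated.

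The size rests on assumed loss counts, assumed CAL risk in lost children, one-sided 5% and a Wald bound. The real number lost is unknown and probably small. The reason to act is that a missed 6-8-week scan cannot be recovered at analysis, and keeping it costs little.

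**What to change.** - In Withdraw criteria (3.2) and Prohibited treatment (3.3), for allergy, a treatment-stopping adverse event, and steroid or biologic rescue, replace trial withdrawal by: *study treatment discontinued; scheduled echocardiograms and safety visits continue*.
- Keep study exit for withdrawn consent, actual loss to follow-up, and criterion 5 where follow-up itself is not feasible. Clinical decisions on stopping or rescue stay with the investigator.
- On the Exit Form add: *study treatment stopped early: yes/no, reason*, separate from study exit.
- In the SAP, analyse these children by allocated arm with their observed CAL status in the ITT analysis, and report treatment stops and withdrawals by arm and reason. A tipping-point analysis for outcomes still missing, with CAL risk varied separately by arm, is optional.

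Cost: an amendment with ethics approval (section 4.2), any matching consent wording and one form field. The scans are already scheduled, and the sample size does not change. The change makes the ITT analysis more complete. It does not repair the per-protocol primary analysis of section 3.11, and the conflict between that section and the SAP is a separate matter.
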